**Data collection, management and quality assurance**

All the information required by the study protocol will be entered on standardized CRFs and surveillance worksheets in French. The Field Investigator will validate all CRFs and surveillance worksheets for completeness and accuracy, signing and dating each to attest to his/her responsibility for the quality of all data recorded and that the data represents a complete and accurate record of each child’s participation in the study. During the study, all CRFs and surveillance worksheets will be maintained at the central study office in a secure location to ensure confidentiality. All validated CRFs and surveillance worksheets will be double-entered, compared and verified for accuracy.

A data validation plan will be prepared before study initiation. Errors will be detected by programs designed to detect missing data or specific errors in the data. These errors will be summarized along with detailed descriptions of the specific problem in a Data Query Report, which will be sent to the Field Investigator for resolution. Written documentation of changes will be available via electronic logs. The primary sponsor will be responsible for maintaining study databases.

**Timeline**

The estimated total duration of the study is one meningitis epidemic season. Given Epicentre and MSF’s established field presence in Niger and experience with performing research in emergency settings, we anticipate 1 month will be used for study preparation, including development of SOPs and ethical/administrative clearance. Once an epidemic has been declared in an eligible district, we anticipate 1 week will be used for recruitment and training of field personnel, and putting in place a facility-based surveillance system. The length of recruitment time will depend on the dynamics of the epidemic, but under the most reasonable assumptions described in Table 2, it should be feasible to include the necessary number of villages over the course of an average-sized epidemic. Analysis and write-up will be completed in the 3 months after study closure.

**SAFETY**

**Documenting serious adverse events**

Passive surveillance for serious adverse events will be conducted from study beginning through 28 days following the last dose of ciprofloxacin administered (whether in the household-level or community-level prophylaxis arm). This surveillance will cover all study participants and be carried out at the health facility-level by study staff.

Serious adverse events (SAEs) are defined as any untoward medical occurrence that at any dose of medicine received results in death, is life threatening, requires inpatient hospitalization or prolongation of existing hospitalization, or results in persistent or significant disability or incapacity, or any medically important event / reaction that may jeopardize the subject and may require medical or surgical intervention to prevent one of the outcomes listed above (Bonhoeffer 2002 and 2004).

SAEs will be defined as an adverse event that at any dose of ciprofloxacin that

1. results in death;
2. is life threatening;
3. requires inpatient hospitalization or prolongation of existing hospitalization;
4. results in persistent or significant disability or incapacity
5. results in congenital malformation or birth defect
6. is medically important event / reaction that may jeopardize the subject and may require medical or surgical intervention to prevent one of the outcomes listed above

Persons who die in a health facility will have events before and at the time of death transcribed from hospital records to determine the cause of death. If death occurs outside of the hospital, cause of death will be established using a standard verbal autopsy form administered to determine the clinical picture and treatment received before death.

SAEs identified will be reported to the Field Investigator within 24 hours of becoming aware of the SAE, whether or not it is considered to be associated with a study intervention. The field team will assemble specific documentation, including medical records and other supporting documents, and will record on the CRF: type of SAE; description of event with time of onset in relation to vaccination and severity; and any medical actions taken and outcome. Where applicable, hospital records and verbal autopsies should be obtained. The dossier will be submitted to the Principal Investigator and Study Monitor for adjudication and determination whether the cases were ciprofloxacin-related. In case of discrepancy between the Principal Investigator and the Study Monitor regarding the causal relationship of ciprofloxacin to an SAE, the Sponsor will designate an independent third party to adjudicate the relationship. All SAEs will be followed up until the event resolves, stabilizes, or is otherwise explained. If an SAE remains unresolved at the time of study closure, a clinical assessment will be made by the Field Investigator and sponsor to determine if continued follow up of the SAE is warranted. All relevant field personnel will be appropriately trained in the reporting and treatment of serious adverse events according to GCP. The National Ethical Committee of Niger will receive a quarterly status report including all notified SAEs during the study. Copies of each report and documentation of IRB notification will be kept in the Trial Master File by the Field Investigator.

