**Ciprofloxacin**

Ciprofloxacin is a fluoroquinolone antibiotic that figures on the WHO list of essential medicines. Ciprofloxacin has a broad spectrum of activity, including against *E.coli,* *Campylobacter* spp*,* *Salmonella* spp, *Shigella* spp, and *P. aeruginosa*, as well as many gram-positive cocci, such as *S. pneumoniae* and *S. aureus*. It is easily absorbed and has good bio-availability. It is commonly used to treat urinary tract infections, skin and soft tissue infections, enterotoxic infections and systemic infections due to *Salmonella* and *Shigella*.

In these cases, it is administered as a several-day course, and it is generally well-tolerated. The most common side effects are gastro-intestinal, and prolonged courses have been associated with *Clostridium difficile* diarrhea.

Historically, concern has existed regarding the use of fluoroquinolones in children, as early reports suggested higher rates of chondrotoxicity and tendinopathy, including rupture of the Achilles tendon. These early associations have since been debunked (Burkhardt, 1997).

Ciprofloxacin is considered a pregnancy category C drug by the United States Food and Drug Administration, meaning that while some evidence of fetal risk has been described in animal studies, no convincing evidence exists in humans. Furthermore, this means that the benefits of treatment may warrant the use of ciprofloxacin despite the potential risks. Ciprofloxacin is the recommended antibiotic for post-exposure prophylaxis to inhalational anthrax, a disease associated with high mortality. For inhalational anthrax, the prophylaxis is for 60 days, and it is recommended for pregnant women in this setting (EMA, 2014). There is therefore a strong precedent for its use as prophylaxis for a potentially life-threatening infection among pregnant women.

Furthermore, ciprofloxacin is recommended by the WHO as an antibiotic prophylactic agent for contacts of meningitis cases in sub-Saharan Africa outside of epidemics (WHO, 2014). WHO

The greatest concern for its use in a mass administration setting would be its potential effect on antibiotic resistance, particularly among enterobacteriaceae.

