In villages selected for the resistance sub-study (in both the standard care arm and community-level prophylaxis arm), participants will be identified at the time of the community sensitization messages being delivered by a study nurse in conjunction with a laboratory technician. A stool sample container will be distributed to each participant, with instructions on how to collect the sample the following morning. Study staff will then return to the village the following morning to collect the fresh stool samples. The same procedures will be followed on days 7 and 28, with one visit to provide the sample container and a second visit to pick up the fresh samples the following morning. Day 0 samples will be collected up until the time of ciprofloxacin administration in the village. At day 7 and 28, samples will also be accepted the day following the scheduled sample collection (i.e., days 8 and 29), if the participant is not able to provide a stool sample on the scheduled day.

*Sample processing*

The processing of stool samples will depend on the location of the study and its distance from the principal study lab in Maradi. The processing of samples will be detailed in the study SOPs. In brief, stool samples will be collected by study staff and either stored at 4°C or inoculated in a transport medium until reception in the central lab. Stool samples will then be plated on a MacConkey agar plate containing ciprofloxacin. After incubation, colonies will be identified using standard microbiological methods. Antibiotic resistance profiles will be determined using the disk diffusion method. The minimum inhibitory concentration (MIC) of relevant antibiotics will be determined. All identified strains will be stored in the Epicentre lab at Maradi. A total of 10% of samples will be sent to a reference laboratory for quality control purposes.

*Participant retention*

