**Assessment of causality**

All SAEs within the first 28 days post-administration of ciprofloxacin will be assessed for a causal relationship with ciprofloxacin by the Principal Investigator / designee. Every effort will be made by the study team to explain each event and assess its causal relationship, if any, to administration of ciprofloxacin. Appropriate medical judgment will be used to determine the causal relationship, considering all relevant factors including the pattern of reaction, temporal relationship, re-challenge, biological plausibility, and confounding factors such as concomitant medication, concomitant disease and relevant history.

The likelihood of the relationship of the event to ciprofloxacin will be recorded as follows:

**Related,** when there is a reasonable possibility that ciprofloxacin contributed to the event.

**Unrelated,** when administration of ciprofloxacin is not suspected to have contributed to the event (CIOMS, 2003).

All post-administration serious adverse events (e.g. those occurring within 30 minutes of administration) will be considered related to ciprofloxacin.

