**Risk minimization and benefits**

All personnel involved in collecting and processing biological samples are trained health care personnel, who will be provided with additional training to avoid or minimize the possibility of any unplanned side effects of these procedures.

The direct benefits individual participants may expect from participating in this study include receiving information about the signs and symptoms of meningitis and information about the free nature of health care during such an epidemic. All participants may also expect to benefit from contacts with members of the study team and the assurance of the best available medical care with close and regular surveillance. Recipients of ciprofloxacin may also potentially benefit from the possible protective effect of the antibiotic against the subsequent development of meningitis. At the population level, an important benefit of obtaining data on the efficacy of the use of ciprofloxacin in response to an epidemic, if proven protective, is the antibiotic potentially being made available for a larger population, particularly in light of current shortages of vaccine against NmC.

To minimize the risk of not reaching the target sample size, starting criteria have been set forth to reduce the possibility of starting the trial too early in an epidemic. Given that reactive vaccination remains the recommended epidemic response for meningitis, all study areas would be evaluated for reactive vaccination by the local health authorities following the usual procedures in place in Niger, and would be eligible for reactive vaccination campaigns. Nonetheless, reactive vaccination campaigns often take 6-8 weeks to organize, so if the proposed study is put into place early in the epidemic, the amount of study inclusion time without this potential confounding factor will be maximized.

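### SAE detection is passive and facility-based while nearly all doses are given in the community: no stated step finds village deaths, and the causality and SAE definitions conflict with the text around them

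*Combined protocol and SAP*

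**What the plan says.** Under Documenting serious adverse events (Safety section), the protocol states that "Passive surveillance for serious adverse events will be conducted from study beginning through 28 days following the last dose of ciprofloxacin administered". The next sentence sets place and coverage: "This surveillance will cover all study participants and be carried out at the health facility-level by study staff". For deaths elsewhere, "If death occurs outside of the hospital, cause of death will be established using a standard verbal autopsy form". That section gives two SAE definitions. The first refers to any dose of a medicine. The second begins "SAEs will be defined as an adverse event that at any dose of ciprofloxacin that" and adds congenital malformation to the list.

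Under Assessment of causality, each SAE in the 28 days after a dose is judged *Related* or *Unrelated*. The section then closes by treating all post-administration SAEs alike: ("e.g. those occurring within 30 minutes of administration) will be considered related to ciprofloxacin".

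Study sites places all distributions in the community. Study procedures (Interventions) makes an exception: household members who accompany a case are offered the drug at the health center or hospital. All doses are directly observed.

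The section on ciprofloxacin says "The most common side effects are gastro-intestinal", but only SAEs are collected. Risk minimization and benefits lists among participants' benefits "the assurance of the best available medical care with close and regular surveillance".

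The resistance sub-study visits 200 people in standard care and 200 in the community-wide arm: "The same procedures will be followed on days 7 and 28, with one visit to provide the sample container and a second visit". The only question described is whether the person received ciprofloxacin. Data analysis contains no safety comparison.

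**The concern.** The place where harm would be seen is not the place where it is looked for. A passive facility system captures an unknown fraction of serious events among people dosed at home, so a low SAE count could mean either few events or few found. The protocol counts all residents of randomized villages as research subjects, at least 20 000 per arm, and offers dosing from infancy upward and in pregnancy.

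Two drafting problems make the data that do arrive harder to use. If every post-dose SAE is automatically related, the causality table carries no information. If an SAE exists only after a ciprofloxacin dose, standard care supplies no comparator for deaths or admissions, although surveillance is said to cover everyone.

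**Working it through.** **1. Detection, text against text.**
- Place of dosing: community (Study sites), except for those accompanying a case (Interventions). The two passages need reconciling.
- Place of SAE surveillance: health facilities, passive.
- Community deaths: a method for establishing cause is given, but no step for learning that a death occurred. The village census (Meningitis surveillance and incidence calculations) is taken once, around the intervention. No repeat enumeration is described.
- Events at dosing: staff are present because doses are observed, but no site-level event record and no observation period is stated.

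**2. Causality sentence.** The 30 minutes is introduced only as an example, so the rule's literal scope is all post-administration SAEs. The preceding text requires a case-by-case judgment over 28 days. Both cannot apply to an SAE on, say, day 10.

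**3. SAE definition.** Coverage is all participants, but the second definition needs a ciprofloxacin dose. Standard-care residents receive none from the study, so their deaths and admissions can fall outside it.

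**4. Deaths at stake.** Assume crude mortality of 5 to 15 per 1000 per year (not in the documents).
- Per 20 000 residents: 20 000 × 0.005 × 28/365 = 7.7, and 20 000 × 0.015 × 28/365 = 23.0 in 28 days.
- Per 200 sub-study participants: 0.08 to 0.23.

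Deaths are therefore numerous enough to compare across arms, but not within the sub-study.

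**5. The plan's own sub-study figure.** The plan gives no size or precision for safety. Its 131 per arm for resistance (20% against 30%, 90% power, two-sided 5%) reproduces:
- n = [1.960√(2 × 0.25 × 0.75) + 1.282√(0.16 + 0.21)]² / 0.10² = 392, and 392/3 visits = 130.7.
- This treats the three samples per person as independent and adds no village effect.
- 131 × 1.25 × 1.20 = 196.5, close to the planned 200.

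The point here does not depend on these figures.

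**6. What symptom questions at Day 7 and Day 28 could show.** Inputs: 200 per arm, 20 per village, 10 villages per arm and 25% attrition (150 left, 15 per village), all from Resistance sub-study. The ICC of 0.025 comes from Sample size, where it is stated for meningitis. Using it for adverse events is an assumption, as are the event rates.

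Effective n = N / [1 + (m − 1) × ICC]:
- 200 / (1 + 19 × 0.025) = 135.6
- 150 / (1 + 14 × 0.025) = 111.1

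Power = Φ{[|p₂ − p₁|√n − 1.960√(2p̄(1 − p̄))] / √(p₁(1 − p₁) + p₂(1 − p₂))}:

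| Assumed rates | n = 135.6 | n = 111.1 |
| --- | --- | --- |
| 5% vs 10% | 0.345 | 0.292 |
| 5% vs 15% | 0.787 | 0.703 |
| Rate detectable against 5%, 80% power | 15.3% | 16.7% |

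Over ICC 0 to 0.05, with and without attrition, the detectable rate runs from 13.0% to 18.5%.

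Zero-event one-sided 95% bound, 1 − 0.05^(1/n):
- Ignoring clustering: 1.5% (n = 200) and 2.0% (n = 150).
- With effective n: 2.2% (135.6) and 2.7% (111.1).

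At an assumed SAE risk of 0.1%, the chance of seeing any in 200 people is 1 − 0.999²⁰⁰ = 18%.

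**The case against.** The case for the plan as it stands is substantial. Safety is not an objective. The protocol argues that a single dose of a well-tolerated drug carries minimal individual risk, and passive SAE-only surveillance of some 60 000 people in an emergency is a reasoned choice. SOPs, CRFs, the consent appendices and parts of the staffing and training text are not available here and may hold more detail. All of this stands. It is why the point asks for stated triggers and corrected wording, not active follow-up of everyone dosed.

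A reader might infer several stronger things that the documents do not support:
- *That every dose is given outside facilities.* Some household-arm doses are offered at a health center or hospital.
- *That village deaths and immediate events have no route in at all.* Doses are directly observed, relevant field staff are trained in SAE reporting, the 24-hour reporting duty runs from awareness, and household-arm nurses return for absentees and new cases. The gap is in defined detection and recording.
- *That the sub-study visits ask nothing.* Receipt of ciprofloxacin is asked; a safety question is not described.
- *That those visits could supply the trial's safety comparison.* They omit the household arm, cover 10 villages per arm, rest on open-label self-report with recall to Day 28, and have little power except for large differences in common events. They do not address missed deaths or immediate events.

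It is also fair that the intent of the causality sentence can be guessed from the paragraph before it. The literal text still needs correcting, because adjudicators will apply it.

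**Conclusion.** The concern holds in this form. For an intervention delivered mainly in the community, the available text gives no step for finding deaths outside facilities and no record of events at dosing. Its causality rule contradicts itself, and one of its two SAE definitions conflicts with the stated coverage. These findings rest on the text alone.

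The size depends on assumptions. Roughly 8 to 23 deaths per 20 000 residents in 28 days are at issue if mortality is 5 to 15 per 1000 per year; how many of them facility surveillance would miss cannot be computed. The symptom questions are worth having only as description, with a detectable rate of about 15–17% against 5% at the borrowed ICC of 0.025. The primary incidence analysis is not affected. Nor do the documents show that harm would be hidden, only that a low SAE count could not be interpreted.

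**What to change.** 1. **Assessment of causality.** Reword so that the automatic *related* label covers only the 30-minute events the sentence names, with every other SAE judged individually. Have distribution staff record any event they see at the site.
2. **Documenting serious adverse events.** Use one dose-independent SAE definition. Make a community death reported by a village chief, a community health worker or a nurse on a repeat visit a trigger for the SAE form and verbal autopsy, in all three arms. Reconcile Study sites with Interventions on where doses are given.
3. **Resistance sub-study, Sample collection (optional, descriptive).** At the existing Day 7 and Day 28 visits, ask the same short set of symptom and admission questions in the standard-care and community-wide arms. Report by arm, allowing for village clustering, and state that the results do not bear on deaths or rare SAEs.

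Cost: item 1 is wording plus a simple site log. Item 2 adds reporting work. Under the assumed mortality range, finding every death among 60 000 residents would mean 3 × 7.7 = 23 to 3 × 23.0 = 69 deaths per 28 days, including those already seen at facilities. Item 3 costs a few minutes per participant and one table, with no new visits or staff. It has the limits of open-label self-report and gives no household-arm data. Changes to procedures need a formal amendment and ethics approval under Protocol amendments, and item 3 may also need revised sub-study consent.

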**Interventions**

Oral ciprofloxacin for household or community contacts of meningitis cases during an epidemic. Community sensitization messages about signs and symptoms of meningitis.

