**Standard care for meningitis**

Throughout the study period, the diagnosis and treatment of meningitis in all health centers in study areas will be provided free of cost to any person, regardless of whether they have participated in a distribution of ciprofloxacin. Health center staff will provide physical examinations, lumbar punctures if necessary, and appropriate antibiotic therapy following national protocols. All patients in study areas who need referral from a health center to the district hospital will be transported free of charge.

Participation in the study will in no way affect the eligibility of a village or a HA for reactive vaccination with a polysaccharide or conjugate vaccine.

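### The SAE form is to time onset from vaccination, which the trial does not give, while the safety window and causality criteria run from ciprofloxacin

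*Combined protocol and SAP*

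**What the plan says.** The section Documenting serious adverse events lists what goes on the case report form for each SAE: its type, a "description of event with time of onset in relation to vaccination and severity", and the actions taken and outcome. This is the only timing item in the list. The same paragraph sends the dossier to the principal investigator and study monitor for "determination whether the cases were ciprofloxacin-related".

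The trial's product is stated under Interventions: "Oral ciprofloxacin for household or community contacts of meningitis cases during an epidemic", alongside sensitization messages. Vaccination enters only from outside the trial. Standard care for meningitis says: "Participation in the study will in no way affect the eligibility of a village or a HA for reactive vaccination".

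The safety rules count from ciprofloxacin. Passive surveillance runs "through 28 days following the last dose of ciprofloxacin administered". Under Assessment of causality, "All SAEs within the first 28 days post-administration of ciprofloxacin will be assessed for a causal relationship with ciprofloxacin", and temporal relationship is named among the factors to weigh. The section adds: "All post-administration serious adverse events (e.g. those occurring within 30 minutes of administration) will be considered related to ciprofloxacin".

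**The concern.** The interval to be recorded is not the interval that the safety rules use. For an unvaccinated person the item has no meaning. For a person vaccinated in a reactive campaign it can be filled with a genuine interval that says nothing about ciprofloxacin. In both cases the adjudicators would lack, on the form, the time from dose to onset that decides membership of the 28-day set and informs the causality judgment. The protocol acknowledges, in its summary of risks, that there are no data on ciprofloxacin as an epidemic response in this region, and SAE surveillance is passive. The timing evidence that is collected should therefore be the right one.

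**Working it through.** There is no planned figure to reproduce. The check compares the clock on the form with the clocks in the rules.

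| Item | Section | Clock starts at |
|---|---|---|
| SAE onset on the form | Documenting serious adverse events | Vaccination |
| End of SAE surveillance (28 days) | Documenting serious adverse events | Last ciprofloxacin dose |
| Set assessed for causality (28 days) | Assessment of causality | Ciprofloxacin administration |
| Automatic relatedness (30 minutes as an example) | Assessment of causality | Ciprofloxacin administration |
| Decision asked of the adjudicators | Documenting serious adverse events | Relatedness to ciprofloxacin |

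The first row disagrees with every other row.

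*Size of the error in one record.* Let C, V and S be the days of ciprofloxacin, vaccination and SAE onset. The form holds S − V and the rule needs S − C. The error is (S − V) − (S − C) = C − V, the gap between the two events, whatever the onset day. It is zero only if both fall on the same day. Write d for the size of that gap and x for the days from the later of the two events to onset, with x at most 28. One interval is x and the other is x + d, so they fall on opposite sides of the 28-day cut when x + d exceeds 28. If d is above 28, that is true of every such SAE. If d is 28 or less, it is true only when x is greater than 28 − d.

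*Three illustrations.* The days are assumptions, because the documents give none.

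| Record | Interval on the form | Interval needed | Against the 28-day cut |
|---|---|---|---|
| Dosed day 0, never vaccinated, SAE day 5 | none | 5 − 0 = 5 | Not classifiable from the item; truly inside |
| Dosed day 0, vaccinated day 45, SAE day 50 | 50 − 45 = 5 | 50 − 0 = 50 | Looks inside; truly outside |
| Vaccinated day 0, dosed day 40, SAE day 45 | 45 − 0 = 45 | 45 − 40 = 5 | Looks outside; truly inside |

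*Is the dose time required anywhere else?* The surveillance section records whether a suspected meningitis case had received a dose, with no date. The resistance sub-study asks participants whether they received the distribution, again with no date. Doses are directly observed in both prophylaxis arms, but no section requires a person-level record of when each was given.

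*Could it be rebuilt?*
- In the community-wide arm each village has a single distribution, so the day might be inferred from the village.
- In the household arm, members may be dosed at the home visit, at the health facility when accompanying the case, or at a return visit if absent. Visits recur with each new case in the village, so one person could have more than one dose date. A village-level date does not settle these.
- An interval in minutes needs a clock time, which no section requests.
- Surveillance covers all study participants, including those never dosed, and the list has no entry for that.

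**The case against.** The strongest reply is that one stray word is being read against all the text around it. The same paragraph asks about ciprofloxacin, the SAE definition refers to ciprofloxacin, and the causality section mentions nothing else. The two references cited for the SAE definition concern adverse events following immunization, which suggests wording carried over from a vaccine protocol. Staff would probably notice. The form itself is not in the documents, only a one-sentence summary of its content; procedures and a data validation plan are still to be written, and the monitor audits the study tools before the start.

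Much of this stands, and more besides:
- Identified SAEs go to the field investigator within 24 hours whether or not they are thought related, and the dossier is adjudicated whatever the onset item says.
- Relatedness rests on medical judgment with timing as one factor, and the 30 minutes is only an example.
- Medical records and supporting documents are assembled, so the dose day may be recoverable.
- Reactive vaccination is possible, not certain, and the background describes scarce vaccine. The 6 to 8 weeks quoted for campaigns is time to organize one, not an interval from anyone's dose.
- No safety objective or safety analysis is defined for this item to bias.

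What does not stand is the step from an obvious slip to a harmless one. The surrounding wording shows that the item is a mistake; it does not supply the missing dose time, and no section orders its reconstruction.

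**Conclusion.** The point holds as a defect in safety recording. Followed as written, the item does not yield time since ciprofloxacin, and after a reactive campaign it may yield an irrelevant interval. The effect is confined to the timing evidence for SAEs among ciprofloxacin recipients. The documents give no SAE rate, so the number of such records cannot be stated.

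Three stronger readings are tempting and are not supported:
- A reader might infer that SAEs within 28 days of dosing would be missed. The onset item does not control detection, reporting or submission for adjudication.
- A reader might infer that relatedness labels would be wrong for anyone vaccinated on another day. The label is a judgment on several factors, not a computation from this interval.
- A reader might take the population expected to be offered ciprofloxacin (over 20 000 in the village-wide arm and several thousand in the household arm, under Informed consent) as the number affected. Only recipients with an SAE have an SAE form.

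The primary comparison of meningitis incidence is untouched. The conclusion assumes that the form follows the protocol's list; a form that already captures each dose date and time would reduce the matter to correcting the protocol text.

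**What to change.** Reconcile the onset item in Documenting serious adverse events with the surveillance window in that section and with Assessment of causality. Replace the reference to vaccination with: date and time of onset, and date and time of each ciprofloxacin administration (or not dosed). Use these fields for the 28-day set and the other timing criteria. Record any vaccination date in a separate field, so that it remains available as a possible alternative explanation.

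The cost is one phrase in the protocol and two or three fields on the SAE form, with no added visits. Dose times need to be noted when doses are observed so that the fields can be filled. The sponsors should decide under Protocol amendments whether this is a clarification by memorandum or a formal amendment.
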